## 1 SYNOPSIS

**Title:** Retrospective survey of patients with hereditary transthyretin-mediated amyloidosis (hATTR) treated with Onpattro® (patisiran-LNP) in real-world clinical practice in Belgium.

**Short Title:** Onpattro® survey

**Sponsor:** Alnylam Pharmaceuticals

**Phase:** Phase IV retrospective chart review.

**Survey rationale:** This retrospective survey will be conducted to collect data needed in the context of the Convention between Alnylam and the Belgian Health Insurance Agency (Rijksinstituut voor Ziekte- en Invaliditeitsverzekering / Institut national d'assurance maladie-invalidité (RIZIV/INAMI) relating to the conditional reimbursement of Onpattro®. The results of this survey will be incorporated in a report to the Belgian Health Insurance Agency and due by June 1st 2021.

The survey aims to gather information about the real-world impact of the reimbursement of Onpattro® on epidemiology, the clinical practice and its associated resource use of adult hATTR patients in Belgium; on the real world usage of Onpattro® and the clinical outcomes associated with its use.

### Objectives:

- Primary:**
- To determine current hATTR patient numbers and clinical practice in terms of treatments used for all Belgian patients included in the total cohort, on 01 Feb 2021.
  - To determine the clinical impact of Onpattro® use in adult patients with hATTR, in real world circumstances, in the Onpattro® subcohort in terms of neurological and cardiac symptoms, for the period starting from 01 July 2018 (start of Expanded Access Program [EAP]), up to 01 February 2021.
  - To establish real-world Onpattro® use for adult hATTR patients treated with Onpattro® in the Onpattro® subcohort, for the period starting from 01 July 2018 (start of EAP), up to 01 February 2021
- Secondary:**
- To determine the clinical impact of Onpattro® use in adult patients with hATTR, in real world circumstances, in the

Onpattro® subcohort in terms of Quality of Life (QOL), for the period starting from 01 July 2018 (start of EAP), up to 01 February 2021.

### Survey Design:

Type of design: observational, retrospective, multi-center, descriptive chart review.

Duration of the survey:

- data collection form completion period: 01 April 2021 to 16 April 2021;
- Onpattro® treatment period covered by the questionnaire: 01 July 2018 to 1 February 2021;
- Data analysis and report: 18 April 2021 to 15 May 2021.

Data Collection: Data collection form completion by investigator (or site personnel).

### Endpoints

#### Primary:

Onpattro® treatment use in terms of:

- Treatment start & stop dates (with reason for stopping)
- Prescribed dosage of Onpattro® (in mg/kg) at the beginning of each cycle
- Total number of Onpattro® vials consumed, at the end of each cycle
- Total number of Onpattro® treatment cycles
- Total number of Onpattro® vials at each timepoint (if available)

Onpattro® treatment compliance in terms of:

- Number of missed Onpattro® treatment cycles per year (if any)
- Treatment interruptions (if any), with dates of treatment discontinuation and treatment reinitiation (with reason for interrupting)

Neurological endpoints:

- FAP score (1, 2) as described by Coutinho (1980)
- EMG status (worsened, stable or improved)
- MRC S-S score (scale of 0-6)
- Functional independence measurements (FIM) score (scale of 1-7)
- NIS score (scale of 0-244)

- ACTIVLIM score (impossible, difficult, easy)
- CADT score (using a scale of 0-4; total normal score of 16 in women and 20 in men)
- VAS score for pain (using a visual analog scale)
- PND score (0, 1, 2, 3a, 3b, 4)

Cardiological endpoints:

- Orthostatic hypotension (yes or no)
- NYHA score (class I-V)
- ECG status (worsened, stable or improved)
- Echocardiography status (worsened, stable or improved) + Cardiac Output percentage

**Secondary:**

QoL endpoints

- EQ5-D score
  - EQ5-D type
  - EQ5-D score
- SF-36 or SF-12 score (transformed to 0-100 scale; higher scores indicate better health-related QoL)

**Target population:** Adult patients with hATTR with polyneuropathy stage 1 or 2.

**Site selection and number:** 7 sites of NeuroMuscular Reference Centers (NMRC) in Belgium of which 5 sites currently have patients treated with Onpattro®.

**Sample size:** Approximately 30 patients in the total cohort (meeting the criteria for inclusion), of which approximately 9-12 patients treated with Onpattro®, in the Onpattro® sub-cohort.

**Inclusion & Exclusion criteria:** Adult patients (≥18 years old) diagnosed with hATTR with polyneuropathy, and confirmed by genetic testing will be included in this survey. There are no specific exclusion criteria.

## 2 LIST OF ABBREVIATIONS AND DEFINITION OF TERMS

The following abbreviations and special terms are used in this protocol.

| Abbreviation | Definition                                       |
|--------------|--------------------------------------------------|
| BMI          | Body Mass Index                                  |
| CATD         | Compound Autonomic Dysfunction Test              |
| CI           | Confidence Interval                              |
| EAP          | Expanded Access Program                          |
| ECG          | Electrocardiogram                                |
| EMG          | Electromyography                                 |
| FAP          | Familial Amyloid Polyneuropathy                  |
| FIM          | Functional Independence Measurements             |
| hATTR        | Hereditary Transthyretin-Mediated Amyloidosis    |
| IEC          | Institutional or Independent Ethics Committee    |
| INAMI        | Institut National d'Assurance Maladie-Invalidité |
| IV           | Intravenous or Intravenously                     |
| LNP          | Lipid Nanoparticle                               |
| MRC S-S      | Medical Research Council Sum-Score               |
| mRNA         | Messenger Ribonucleic Acid                       |
| mBMI         | Modified Body Mass Index                         |
| mNIS         | Modified Neuropathy Impairment Score             |
| NIS          | Neuropathy Impairment Score                      |
| NYHA         | New York Heart Association                       |
| OLT          | Orthotopic Liver Transplantation                 |
| PND          | Polyneuropathy Disability                        |

| Abbreviation | Definition                                              |
|--------------|---------------------------------------------------------|
| QoL          | Quality of Life                                         |
| QOL-DN       | Quality of Life – Diabetic Neuropathy                   |
| RIZIV        | Rijksinstituut voor Ziekte- en Invaliditeitsverzekering |
| RNA          | Ribonucleic Acid                                        |
| RNAi         | Ribonucleic Acid Interference                           |
| TTR          | Transthyretin                                           |
| VAS          | Visual Analog Scale                                     |

### 3 LIST OF TRADEMARKS

Onpattro®

## 5 BACKGROUND INFORMATION AND SCIENTIFIC RATIONALE

### 5.1 Background

Hereditary transthyretin-mediated amyloidosis (hATTR) is a rare, life-threatening, autosomal dominant multi-systemic disease caused by mutations in the transthyretin (TTR) gene that results in progressive, chronically debilitating morbidity and mortality. The estimated European prevalence of hATTR is 0.14 per 10,000 (between 5000 to 6000 patients), with the majority of cases in Portugal, France, Italy, and the United Kingdom [Patisiran].

There are over 120 reported TTR genetic mutations associated with hATTR, and almost all patients are heterozygous for the mutated TTR allele [Connors, 2003; Falk, 2012; Ando, 2013]. Historically, two clinical syndromes of hATTR have been described: familial amyloidotic polyneuropathy (FAP), and familial amyloidotic cardiomyopathy, both of which are characterized by amyloid deposits comprised of both mutant and wild-type TTR [Yazaki, 2000].

The clinical manifestations of the length-dependent, symmetrical sensorimotor neuropathy are the result of amyloid-mediated injury to large and small peripheral nerve fibers. Sensory abnormalities include painful dysesthesias in the feet and hands, as well as loss of sensation leading to thermal burns involving the feet and hands and to joint injury in the lower limbs. Progressive muscle atrophy and motor weakness in both lower and upper limbs leads to impairment of ambulation and inability to perform other activities of daily living such as holding eating utensils or a drinking glass or managing buttons and zips. Autonomic dysfunction results in debilitating orthostatic hypotension, severe gastrointestinal symptoms (including early satiety, chronic nausea/vomiting, and both diarrhea and constipation), bladder dysfunction with dysuria and urinary retention, as well as cardiac arrhythmias [Connors, 2004; Plante-Bordeneuve, 2011; Ando, 2013]. Cardiac infiltration with amyloid leads to cardiomyopathy characterized by heart failure due to both diastolic and systolic dysfunction, conduction disturbances and arrhythmias [Connors, 2004; Benson, 2007; Plante-Bordeneuve, 2011; Ando, 2013; Swiecicki, 2015]. This constellation of progressive morbidity results in severe disability, wasting due to gastrointestinal malabsorption and malnutrition, and profound loss of quality of life. Death usually results from heart failure or infection, with a median survival of 4.7 years (range 1.3 to 24.8 years) following diagnosis [Plante-Bordeneuve, 2011; Swiecicki, 2015].

In terms of symptoms, four stages of hATTR with polyneuropathy (FAP stages) are distinguished. Patients with stage 0 disease are asymptomatic, patients with stage I (mild) disease are ambulatory, patients with stage II (moderate) disease are ambulatory but require assistance, and patients with stage III (severe) disease are bedridden or wheelchair-bound [Ando, 2013].

Since many of the systemic manifestations of the disease are caused by liver-derived circulating TTR, several treatment approaches aimed at reducing the amount of circulating amyloidogenic protein are currently used for hATTR: orthotopic liver transplantation (OLT), TTR tetramer stabilizers (including tafamidis) and gene silencing by ribonucleic acid interference [RNAi].

Onpattro® is a synthetic RNAi therapeutic, containing patisiran (ALN-18328), a small interfering RNA targeting TTR messenger RNA (mRNA) formulated as lipid nanoparticles (LNP) to target delivery to hepatocytes in the liver, the primary source of TTR protein in the circulation. The therapeutic hypothesis is that the reduction of liver-derived circulating amyloidogenic TTR protein by Onpattro® will reduce the deposition and promote the stabilization or clearance of TTR amyloid deposits, thereby stabilizing or improving the disease manifestations including polyneuropathy and cardiomyopathy and improving overall health.

Efficacy data were collected in 3 core studies in patients with hATTR with polyneuropathy, including a randomized (2:1 Onpattro® to placebo), double-blind, placebo-controlled Phase 3 study called APOLLO (Study 004), a Phase 2 open-label, single-arm, long-term follow-up extension study (Study 003), and a open-label, single-arm, long-term follow-up extension study for patients completing Study 004 or Study 003 (Study 006). Across all 3 studies, Onpattro® was administered as an approximately 80-min intravenous (IV) infusion at a 300 µg/kg dose every 3 weeks, and all patients were administered premedication (including corticosteroids, H1 and H2 blockers, and paracetamol) to reduce the risk of infusion related reactions.

The pivotal Phase 3 APOLLO study enrolled 225 patients (global 148 on patisiran-LNP and 77 on placebo) [Adams, 2018]. Patients were randomized at 44 sites in 19 countries from North America, Europe, Asia Pacific and Central/South America from December 2013 through January 2016. APOLLO was designed to assess the effect of patisiran-LNP relative to placebo on neuropathy and cardiomyopathy. The primary efficacy endpoint was change from baseline in the mNIS+7 composite neurologic impairment score (NIS) at 18 months. Secondary endpoints included quality of life (Norfolk Quality of Life – Diabetic Neuropathy [QOL-DN] score), measures of motor strength (Neurologic Impairment Score – Weakness), disability (Rasch-built Overall Disability Scale), gait speed (10-meter walk test), nutritional status (calculation of modified body mass index [mBMI]) and autonomic symptoms (Composite Autonomic Symptom Scale-31).

APOLLO met its primary endpoint, modified NIS (mNIS)+7. An improvement in neuropathy compared to baseline (mNIS+7 change of <0 points) at 18 months was seen in 56.1% (95% confidence interval [CI]: 48.1%, 64.1%) of patients on Onpattro® compared to only 3.9% (95% CI: 0.0%, 8.2%) on placebo (odds ratio of 40.0,  $p=1.82 \times 10^{-15}$ ). The effect of Onpattro® on mNIS+7 was observed across all patient subgroups defined by age, sex, ethnicity, geographic region, TTR genotype, neuropathy severity, disease stage, prior TTR tetramer stabilizer use and cardiac subpopulation. APOLLO also met all of its secondary endpoints, including the key secondary endpoint of Norfolk QOL-DN [Adams, 2018].

Onpattro® received a marketing authorisation in the European Union on 27 August 2018 for the treatment of hATTR. An Expanded Access Program (EAP), was launched on 01 July 2018, to allow patients with hATTR to receive Onpattro®. Onpattro® received a temporary reimbursement from Belgian Health Insurance Agency (Rijksinstituut voor Ziekte- en Invaliditeitsverzekering / Institut national d'assurance maladie-invalidité [RIZIV / INAMI]) on 01 December 2019.

The recommended dose of Onpattro® is 300 µg/kg administered via intravenous infusion once every 3 weeks. Dosing is based on actual body weight. For patients weighing ≥100 kg, the recommended dose is 30 mg. Vitamin A supplementation at approximately 2500 IU vitamin A per day is advised for patients treated with Onpattro®.

## 5.2 Survey rationale

This retrospective survey will be conducted in order to collect data needed in the context of the Convention between Alnylam and the Belgian Health Insurance Agency (Rijksinstituut voor Ziekte- en Invaliditeitsverzekering / Institut national d'assurance maladie-invalidité [RIZIV / INAMI]) when granting prolongation of the reimbursement of Onpattro®. The results of this survey will be incorporated in a report to the Belgian Health Insurance Agency and due by June 1st 2021.

The survey aims to gather information about the real-world impact of the reimbursement of Onpattro® on epidemiology, the clinical practice and its associated resource use of adult hATTR patients in Belgium; on the real world usage of Onpattro® and the clinical outcomes associated with its use.

## 6 OBJECTIVES

### 6.1 Primary objective(s)

- To determine current hATTR patient numbers and clinical practice in terms of treatments used for all Belgian patients included in the total cohort, as on 01 Feb 2021.
- To determine the clinical impact of Onpattro® use in adult patients with hATTR, in real world circumstances, in the Onpattro® subcohort in terms of neurological and cardiac symptoms, for the period starting from 01 July 2018 (start of EAP), up to 01 February 2021.
- To establish real-world Onpattro® treatment use for adult hATTR patients treated with Onpattro® in the Onpattro® subcohort, for the period starting from 01 July 2018 (start of EAP), up to 01 February 2021.

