## 8.2 Inclusion/exclusion criteria for patients

Inclusion criteria: adult patients ( $\geq 18$  years old) with a diagnosis of hATTR with polyneuropathy, confirmed by genetic testing.

Exclusion criteria: there are no specific exclusion criteria.

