**Cardiological endpoints:**

- Orthostatic hypotension (yes or no)
- NYHA score (class I-V)
- ECG status (worsened, stable or improved)
- Echocardiography status (worsened, stable or improved) + Cardiac Output percentage

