**11.2 Cohorts**

The total cohort will include all patients meeting the inclusion criteria (i.e. with a diagnosis of hATTR confirmed by genetic testing), for which aggregated data will be collected.

The Onpattro® sub-cohort will include patients with hATTR that have been treated with Onpattro® from the start of the Expanded Access Program (EAP) in 01 July 2018, up to 01 February 2021, for which individualized data will be collected.

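### ECG and echocardiography are coded only as change in a sub-cohort selected on polyneuropathy, so 'stable' mixes patients without heart disease with patients whose heart disease was stabilised

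*Protocol*

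**What the plan says.** Section 6.1 sets the cardiac part of the second primary objective for the whole treated group: "in the Onpattro® subcohort in terms of neurological and cardiac symptoms". Section 8.2 admits adults "with a diagnosis of hATTR with polyneuropathy, confirmed by genetic testing" and adds "Exclusion criteria: there are no specific exclusion criteria". Section 11.2 narrows this by treatment only: "The Onpattro® sub-cohort will include patients with hATTR that have been treated with Onpattro" within the observation window. No cardiac subset is defined. Section 8.1 expects about 9-12 such patients.

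Section 11.1.1 lists four cardiological endpoints. Two are states at a timepoint: NYHA class and "Orthostatic hypotension (yes or no". The ECG entry is a change code, "ECG status (worsened, stable or improved". Echocardiography has the same three change codes plus a cardiac output percentage.

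Table 1 in section 9.2 schedules all four at EAP treatment initiation, first reimbursement, reimbursement prolongation and last evaluation. It has no row for cardiac involvement.

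Section 5.1 does not treat heart disease as universal. It describes a polyneuropathic and a cardiomyopathic syndrome, and it lists "prior TTR tetramer stabilizer use and cardiac subpopulation" among the subgroup factors of the pivotal study.

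**The concern.** A patient whose heart is normal at every visit has only one ECG and echocardiography code available: 'stable'. A patient whose cardiac disease stopped progressing gets the same code. The two mean different things for a question about the drug's cardiac impact.

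The code matters because section 5.1 counts stabilisation of cardiomyopathy, as well as improvement, among the results expected of treatment. 'Stable' will therefore read as favourable. Section 7 specifies one group and no comparator, and section 5.2 says the results go to the health insurer in connection with prolonged reimbursement. That reader would have nothing against which to judge a high 'stable' frequency.

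There is also a difficulty at the first timepoint. A change code needs an earlier reference, and none is stated. At treatment initiation the code either has no meaning or refers to an unspecified earlier examination. In neither case does it give the baseline state of the heart.

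**Working it through.** The protocol gives no figure to reproduce: section 11.3 plans descriptive summaries only, and section 11.4 makes no power calculation. The check has two parts.

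**1. Can cardiac involvement at start be read from the form?**

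| Item at start | What it gives | Does it identify involvement? |
|---|---|---|
| NYHA class | Functional state | Partly; a higher class is informative, but no rule links class to involvement |
| Orthostatic hypotension | Yes/no state | Weakly; section 5.1 says "Autonomic dysfunction results in debilitating orthostatic hypotension" |
| Cardiac output percentage | Numeric value | Partly; no threshold is given |
| ECG status | Change code | No |
| Echocardiography status | Change code | No |

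Involvement is incompletely derivable: some patients could be classified, but not all of them reliably.

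**2. What does the mixture do to the summaries?**

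Let *p* be the share of the sub-cohort with cardiac involvement, *w* the share of involved patients who worsen, and *i* the share of involved patients who improve. Assume that unaffected patients are all coded 'stable'. The documents give none of these values.

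- Not worsened, sub-cohort: 1 − *p*·*w*. Among involved: 1 − *w*. Difference: *w*(1 − *p*).
- Improved, sub-cohort: *p*·*i*. Among involved: *i*.

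For assumed *p* of 0.3 to 0.7 and *w* of 0.4 to 0.5:

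| *p* | *w* | Sub-cohort, 1 − *p*·*w* | Involved, 1 − *w* | Difference |
|---|---|---|---|---|
| 0.3 | 0.4 | 0.88 | 0.60 | 0.28 |
| 0.3 | 0.5 | 0.85 | 0.50 | 0.35 |
| 0.7 | 0.4 | 0.72 | 0.60 | 0.12 |
| 0.7 | 0.5 | 0.65 | 0.50 | 0.15 |

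The sub-cohort figure is 65-88% against 50-60% among involved patients. These are unrounded proportions. With about three involved patients, one patient is a third of the group, so whole-patient counts would scatter more widely.

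A count example shows both directions. Take 12 patients, 6 of them unaffected; of the 6 involved, 2 worsen, 2 are stable and 2 improve.

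| | All 12 | 6 involved |
|---|---|---|
| Not worsened | 10/12 = 83% | 4/6 = 67% |
| Stable | 8/12 = 67% | 2/6 = 33% |
| Improved | 2/12 = 17% | 2/6 = 33% |
| Worsened | 2/12 = 17% | 2/6 = 33% |

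Both 'improved' and 'worsened' are diluted toward 'stable'. If *p* = 1, there is no difference. If unaffected patients can develop heart disease at a rate *v*, the sub-cohort figure becomes 1 − *p*·*w* − (1 − *p*)·*v*. It still exceeds 1 − *w* whenever *p* is below 1 and *v* is smaller than *w*.

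**The case against.** The strongest reply is that cardiac data at start are scheduled. Table 1 marks all four cardiac parameters at initiation, NYHA class and orthostatic hypotension are absolute states, and echocardiography carries a number. This is correct. A reader might infer that baseline cardiac status goes unrecorded or cannot be derived at all, and the documents do not support that. What remains is that these items are imperfect markers, and that the two test-status codes, which could have shown a normal or abnormal heart, do not.

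Second, a reader might infer that the plan inflates the drug's cardiac benefit. That goes too far. No effect estimate, test or comparator is planned, and the protocol names no 'stable or improved' summary. The mixture flatters 'stable' and 'not worsened' but understates 'improved'. Nor is an unaffected patient bound to be coded 'stable': new heart disease could be coded 'worsened'.

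Third, since section 5.1 describes orthostatic hypotension as autonomic, one might want it moved to the neurological endpoints. It is reported as a separate yes/no item and enters no composite, so moving it would change no result. It is not part of this point.

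Fourth, the matter might be left to the analysis stage. An analysis cannot split by a variable the form does not collect, and section 11.3 says that no formal analysis plan is set out.

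The objection about small numbers stands. With 9-12 patients, split frequency tables will be thin, and patient listings are the realistic format.

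**Conclusion.** The point holds as a limitation of coding and data collection. A primary objective on cardiac symptoms is summarised over patients selected for polyneuropathy, and the ECG and echocardiography codes cannot separate an unaffected heart from a stabilised one. The other baseline items close this gap only in part.

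On the assumed inputs, the sub-cohort 'not worsened' figure lies 12 to 35 percentage points above the figure among involved patients. That range rests on assumed involvement and worsening rates and on unaffected patients all being coded 'stable'. The actual share of unaffected patients is unknown, and the distortion disappears if it is zero. The documents support neither a one-sided claim of exaggerated benefit nor a claim that the survey as a whole is invalid. Correcting the form is a cheap improvement that changes what the cardiac results can be taken to show.

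**What to change.** At treatment start (EAP initiation, or first reimbursement for patients not in the EAP), add to Table 1:

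- cardiac involvement, yes/no, as documented in the chart;
- ECG normal/abnormal and echocardiography normal/abnormal.

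State that this timepoint is the reference for all later worsened/stable/improved codes, and do not use those codes at the start itself. Report NYHA class, ECG and echocardiography by baseline involvement, as counts or individual listings. Show new involvement among initially unaffected patients separately.

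The cost is a few fields taken from charts that are already open for data collection, plus a written amendment approved by the sponsor and ethics committee under section 12.2. The drawback is very small denominators, so the cardiac results should be presented as counts with the group size visible, not as percentages alone.
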